## Abstract

**Introduction:**

Mpox remains an ongoing global health concern, driven by an ongoing clade I outbreak in Central Africa, which has caused substantial morbidity and mortality. Despite deployment of the Modified Vaccinia Ankara-Bavarian Nordic (MVA-BN) vaccine, data on the durability of vaccine-induced immune responses remain limited, particularly in African populations, women and people with HIV, highlighting the need for context-specific immunogenicity data.

**Methods and analysis:**

Mpox-Vax AFRIVAC is a prospective, multicentre observational cohort study conducted in Uganda, Tanzania and the Democratic Republic of the Congo (DRC). Adults eligible for MVA-BN vaccination for mpox prevention or who received a first dose within 28 days prior to enrolment are followed for 48 weeks. Serial blood samples are collected to quantify binding antibody responses and assess their durability over time. The primary outcomes are mean geometric MVA-BN-specific antibody titres at week 48 and the rate of antibody decay from week 6 to week 48. Secondary outcomes include antibody kinetics at intermediate time points, factors associated with immune responses, breakthrough infection and vaccine safety. Analyses will use descriptive and longitudinal statistical methods to evaluate immune response trajectories and associated host factors, including HIV status, age and sex.

**Ethics and dissemination:**

The study is conducted in accordance with the Declaration of Helsinki, registered at the Pan African Clinical Trials Registry (PACTR202601855406764) and publications will be in accordance with the recommendations of the International Committee of Medical Journal Editors. The study has received ethical approvals in Uganda, DRC and Tanzania. Approval for Uganda has been obtained from Uganda Virus Research Institute Research and Ethics Committee (GC/127/1062) and Uganda National Council for Science and Technology (HS5575ES), for DRC from the Institutional Committee of Health ethics (UCB/CIES/PB/001/2025) and for Tanzania from the National Institute for Medical Research (NIMR/HQ/R.8a/Vol.IX/5187).

**Trial registration number:**

PACTR202601855406764.

STRENGTHS AND LIMITATIONS OF THIS STUDYThis is a prospective multicentre cohort study conducted across African countries directly affected by the ongoing clade Ib mpox outbreak.Predefined recruitment quotas are used to ensure representation of women and people with HIV.Serial longitudinal sampling over 48 weeks enables assessment of the durability of Modified Vaccinia Ankara-Bavarian Nordic-induced antibody responses using harmonised methods across African and European cohorts.Standardised serological testing is performed using a validated quantitative electrochemiluminescence immunoassay.As an observational study embedded within standard-of-care vaccination programmes, causal inference regarding vaccine effectiveness is limited.

## Introduction

 Mpox infections, caused by the Monkeypox virus (MPXV), remain a major and evolving global public health challenge. In May 2022, an unprecedented outbreak marked the first sustained autochthonous transmission of clade IIb MPXV in non-endemic regions, prompting the WHO to declare mpox a Public Health Emergency of International Concern (PHEIC) in July 2022.^1^ To date, over 100 000 cases of clade IIb mpox have been reported, with transmission occurring predominantly through sexual contact among gay and bisexual men who have sex with men (gbMSM).^2^ In parallel, an outbreak of clade Ib MPXV in Central Africa has intensified and has resulted in almost 65 000 cases and a reported case fatality ratio of 2.3% in endemic regions.^3^ In contrast to the 2022 outbreak, women have accounted for more than half of those affected.^4^ This led the WHO to declare a second PHEIC in August 2024, establishing the African outbreak as a dominant global public health priority.^5^

In the context of the PHEIC a third-generation non-replicating smallpox vaccine, Modified Vaccinia Ankara-Bavarian Nordic (MVA-BN), received emergency use authorisation for mpox pre-exposure and postexposure prophylaxis. Short-term immunogenicity data from phase I–III clinical trials demonstrated robust antibody responses,^6–8^ and observational studies from the clade IIb outbreak have estimated that two doses confer substantial protection against mpox infection.^9^ However, these data are largely limited to early postvaccination time points and predominantly reflect populations affected during the 2022 outbreak, namely Caucasian gbMSM in high-income, non-endemic settings. As a result, their generalisability to African populations affected by clade Ib MPXV remains uncertain.

Emerging evidence indicates that circulating and neutralising antibody responses induced by MVA-BN vaccination may wane substantially within 2 years postvaccination, raising concerns about durability of vaccine-induced protection.^10–13^ Consistent with this, increasing reports of breakthrough mpox infections in vaccinated individuals further underscore uncertainty surrounding the longevity of protective immunity.^14
15^ These concerns take on particular significance in settings where host factors may accelerate immune decay, notably in regions with a high prevalence of HIV such as Uganda and the Democratic Republic of the Congo (DRC).^16
17^ Several studies have demonstrated that people with HIV (PWH) exhibit lower peak binding and neutralising antibody titres following MVA-BN vaccination, more rapid antibody decay and associations between reduced CD4+ T cell counts and impaired humoral responses.^10
18–20^ This is especially concerning given that PWH experience a disproportionate burden of severe mpox disease and mortality.^21^ Despite this, data on vaccine immunogenicity in African populations, women and individuals with immunosuppression remain extremely limited.

Understanding the durability of immune responses following mpox vaccination in the populations most affected by ongoing transmission is essential to inform public health policy. Such data are required to optimise vaccination schedules, determine the need for booster doses and identify subgroups at increased risk of waning immunity. Without robust, context-specific immunogenicity data, vaccination strategies risk being extrapolated from populations with fundamentally different epidemiological and immunological profiles.

The MpoxVax AFRIVAC study is a prespecified African extension of the MpoxVax phase IV clinical trial in Ireland (EUCT number: 2023–5 07 881-19-00), implemented using harmonised protocols while addressing region-specific epidemiological and immunological questions in areas affected by the ongoing clade I mpox outbreak. Leveraging established clinical research infrastructure across multiple African sites, this prospective cohort study aims to evaluate the durability of MVA-BN specific antibody responses up to 1 year following vaccination and to identify host and clinical factors associated with immune response kinetics in an African population at risk of mpox.

## Objectives

### Primary objective

To assess the rate of change (durability) of, and with, Orthopoxvirus (OPXV)-specific antibodies at week 48 post first vaccination with MVA-BN.

### Secondary objectives

To determine the:

The baseline seroprevalence of OPXV-specific antibodies consistent with prior mpox infection at week 0.The development of OPXV-specific binding antibody responses at week 4 and week 6 following MVA-BN vaccination.To assess the durability of OPXV-specific antibodies at week 24, measured as geometric mean antibody titres and fold-change from week 6.Demographic and clinical factors associated with OPXV-specific antibody responses and durability at week 48 postvaccination with MVA-BN.To assess the rate of change (durability) of OPXV-specific antibodies at week 48 post first vaccination with MVA-BN in understudied populations, including women and people with HIV.The prevalence of asymptomatic seroconversion consistent with incident mpox infection by week 48 postvaccination.To describe the frequency and severity of adverse events following MVA-BN vaccination through week 48.

## Methods and analysis

### Study design

This is a prospective, multicentre observational cohort study evaluating immune responses following administration of the MVA-BN vaccine for prevention of mpox infection. Participants will be enrolled either prior to receipt of the first MVA-BN dose or within 28 days following receipt of the first dose administered as part of standard-of-care vaccination programmes. The study was designed as a prespecified African extension of the MpoxVax phase IV clinical trial currently underway in Ireland to characterise the magnitude and durability of vaccine-induced immune responses over a 48-week follow-up period and to identify host factors associated with immunogenicity in an African setting.

### Study setting

Participants will be recruited from mpox vaccination centres established by ministries of health in mpox-affected regions in three African countries: Uganda, Tanzania and the DRC. The mpox vaccination centres have been established by ministries of health based on the prevailing epidemiological data in the study countries and thus are mpox hotspots where there is an increased risk of mpox transmission. The vaccination exercise by the ministries of health is targeting high risk individuals such as PWH, sex workers among others. Clinical assessments and follow-up will be conducted at Makerere University Lung Institute (MLI) in Uganda, the National Institute for Medical Research (NIMR) in Tanzania and the Catholic University of Bukavu in the DRC. Laboratory processing will be done at local laboratories, and centralised immunological analyses will be conducted at the Uganda Virus Research Centre in Uganda and the Centre for Experimental Pathogen Host Research, University College Dublin.

### Participant recruitment and enrolment

Participants will be recruited at the ministry of health vaccination centres established in mpox hotspots identified through national surveillance. The study teams will work closely with the vaccination teams and community mobilisers to boost recruitment. Eligibility of the participants will be verified through vaccination cards, registration forms and national electronic vaccination records where available. Recruitment quotas have been predefined to ensure adequate representation of women and PWH, who are among the most affected in the ongoing clade 1b mpox outbreak. The study population has an a priori quota of:

25% participants who are people with HIV.50% female participants.

Written informed consent will be obtained from all participants by trained study staff prior to enrolment using participant information materials provided in appropriate local languages, with verbal explanation to ensure understanding. Consent will be documented in accordance with regulatory requirements.

### Eligibility criteria

#### Inclusion criteria

In order to be eligible for participation in the study, the individuals must be:

Adults aged 18 years or older.Eligible for MVA-BN vaccination for mpox prevention as per the national guidelines or have received the first dose of MVA-BN within 28 days prior to enrolment.Able to understand the study procedures, comply with the study procedures and voluntarily agree to participate by giving written informed consent for the trial.

#### Exclusion criteria

Individuals will be excluded if they:

Are unable or unwilling to provide informed consent.Have contraindications to MVA-BN vaccination.Have known hypersensitivity to vaccine components.Are pregnant or breastfeeding at screening.Have clinical signs or prior laboratory-confirmed diagnosis of mpox.Are participating in another interventional vaccine or therapeutic study.These exclusions will be aligned with national vaccination guidance and existing safety data.

### Study medication

The MVA-BN vaccine will be administered by the ministry of health vaccination teams as part of standard-of-care for mpox response. As this will be given outside of study activities, this study is considered an observational study. National Ministry guidelines recommended one dose of 0.5 mL of MVA-BN administered subcutaneously, with consideration of a second dose approximately 4 weeks later if sufficient vaccine stocks became available. However, due to vaccine supply constraints during the study period, all participants in this cohort received a single dose of MVA-BN only. No study-mandated modifications to vaccination schedules will be introduced. The vaccine brand, batch number, administration route, site and date will be recorded for all participants.

### Study procedures

Participants will attend up to five scheduled study visits over a 48-week follow-up period, with the number and timing of visits determined by vaccination status at enrolment. The scheduled visits will include baseline, early postvaccination, intermediate and long-term follow-up assessments. At each visit, clinical data will be collected, including mpox exposure history, symptoms, medical history, concomitant medications and adverse events. HIV-related clinical variables, including antiretroviral therapy status and history of advanced HIV disease (defined as CD4+ T cell count <200 cells/mm³), will be collected for all participants living with HIV. Blood samples will be obtained at all scheduled visits for immunological analyses. Unscheduled visits are permitted at any time for the assessment of suspected mpox infection or adverse events.

For participants enrolled prior to receipt of the first MVA-BN dose, the baseline (week 0) visit will be aligned as closely as possible to the date of first vaccination, followed by visits at weeks 4, 6, 24 and 48 postvaccination. A detailed schedule of visits and procedures for these participants is shown in figure 1.

**Figure 1 F1:**
[figure not shown]
Schedule of visits. Subjects will attend a total of five clinical trial visits over 48 weeks of study as outlined in the schedule of visits above. Visit 2 should be scheduled within a window period of ±3 days, visit 3 within a window period of ±7 days, while visit 4 and visit 5 should be scheduled within a window period of ±2 weeks. Week 0 will align as closely as possible to the date of the first vaccination dose. Week of visit is calculated post date of first MVA dose. *Unscheduled visit to facilitate diagnosis and evaluation of mpox (vaccine failure cases) or evaluation of adverse events. Unscheduled visits will include clinically indicated laboratory testing and if mpox is suspected, biobanking of plasma, serum and PBMCs and swab of mpox lesions for future related work. AE, adverse event; MVA-BN, Modified Vaccinia Ankara-Bavarian Nordic; PBMC, peripheral blood mononuclear cell.

Participants who will have received their first MVA-BN dose within 28 days prior to enrolment will not undergo a week 0 visit. In these participants, the week 4 visit will constitute the first study visit, followed by visits at weeks 6, 24 and 48 postvaccination, as detailed in the online supplemental appendix.

Participant retention strategies include engagement through community mobilisers and local study teams, flexible visit scheduling within predefined visit windows (figure 1) and ongoing communication with participants throughout follow-up. Risk Communication and Community Engagement (RCCE) teams and Community Advisory Boards (CABs) at participating sites will also support participant engagement and retention during the study period. These activities were designed to support participant trust, address vaccine-related misconceptions and facilitate long-term retention during the 48-week follow-up period.

### Study timeline

Recruitment commenced in Uganda and the DRC in January 2025 following completion of regulatory approvals and site initiation activities. Although regulatory approvals were obtained in all participating countries, participant recruitment in Tanzania did not proceed due to limited vaccine availability. Enrolment is complete, with final participant follow-up anticipated to be completed in June 2026.

### Safety monitoring

Adverse events will be collected at all study visits through participant self-reporting and clinical assessment. Serious adverse events and suspected unexpected serious adverse reactions will be reported to sponsors and regulatory authorities in accordance with Good Clinical Practice (GCP) and national regulations.

### Laboratory procedures

Blood samples will be collected at each visit for serological and cellular immune analyses, including plasma, serum and peripheral blood mononuclear cells (PBMCs). Lesion swabs will be collected when clinically indicated for mpox PCR testing and biobanking. Samples will be processed locally and stored in monitored biobanking facilities prior to shipment for central analysis at Uganda Virus Research Institute.

Antibody responses will be quantified using a validated quantitative immunoassay developed at the Centre for Experimental Pathogen Host Research. This electrochemiluminescence assay measures IgG titres to three OPXV antigens (MPXV B6R, MPXV A27L and VACV B5) and has been previously validated for the quantification and differentiation of antibody responses following mpox infection and MVA-BN vaccination.^12^

Functional neutralisation assays, gene expression analyses and additional cellular immunological analyses may be performed on selected subsets of stored samples in future studies. PBMC samples are being prospectively collected to support exploratory cellular immunological analyses in selected participant subsets and for future ethically approved ancillary studies related to mpox immunology and vaccine responses. Sample subsets will be selected to ensure representation across key clinical and demographic groups and longitudinal study timepoints.

### Endpoints

#### Primary endpoint

Mean geometric OPXV-specific antibody titres at week 48 post vaccination with MVA-BN in a population recruited in Africa.Mean rate of change in OPXV-specific antibody titres post week 6 to week 48 in a population recruited in Africa.

#### Secondary endpoints

Proportion of participants with detectable OPXV-specific binding IgG at week 0 consistent with prior mpox infection.Mean geometric OPXV-specific antibody titres at week 4 and week 6 post MVA-BN vaccinationMean geometric OPXV-specific IgG titres at week 24 and fold-change from week 6.Association between predefined demographic and clinical variables and OPXV-specific antibody titres at week 48.Mean geometric OPXV-specific antibody titres at week 48 post vaccination with MVA-BN in women and in PWH and mean rate of change in OPXV-specific antibody titres post week 6 to week 48 in women and in PWH.Proportion of participants with serological evidence of incident mpox infection between week 0 and week 48.Proportion of participants reporting any adverse event and severity within each follow-up interval (0–4, 4–6, 6–24, 24–48 weeks).

### Sample size

We aim to have a 95% chance of obtaining a 90% CI (ie, an overall probability of achieving the desired precision and capturing the true mean with power of 0.95×0.9) whose half-width is at most 50 GMT. Assuming an expected SD of 485 GMT at week 48 (based on simulations using data from the Pittman *et al* phase III efficacy trial of MVA-BN vaccine),^8^ a sample size of approximately 300 participants would be required to achieve the desired level of accuracy around the mean GMT at week 48. To account for a potential 9% dropout rate, 330 participants will be recruited across three clinical sites.

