### Primary endpoint analysis

The primary objective of the study is to assess the durability of, and factors associated with, MVA-BN-specific antibodies at week 48 following a single vaccination dose. The primary endpoints of this study are

Mean geometric OPXV-specific antibody titres at week 48 postvaccination with MVA-BN in a population recruited in Africa.Mean rate of change in OPXV-specific antibody titres from week 6 to week 48 in a population recruited in Africa.

Antibody titres measured from baseline through Week 48 will be analysed using a linear mixed-effects model with log-transformed antibody titres as the dependent variable. To reflect the expected biological pattern of antibody titres following vaccination, time will be modelled as a continuous variable with a prespecified change point at week 6. This specification allows separate linear components for the expansion phase (baseline to week 6) and the waning phase (week 6 to week 48). Week 6 was selected a priori as the change point as this time point is expected to approximate peak vaccine-induced antibody responses following MVA-BN vaccination, thereby separating the early antibody expansion phase from the subsequent waning phase. The model will include fixed effects for time in each interval and a random intercept to account for within-participant correlation arising from repeated measurements.

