The slope corresponding to the week 6 to week 48 interval will represent the primary durability parameter. An unstructured covariance matrix will be used to model the correlation among repeated measures within participants. If the unstructured covariance model fails to converge, alternative covariance structures, such as Toeplitz or heterogeneous first-order autoregressive (AR(1)), will be considered. Selection among competing covariance structures will be guided by the Akaike information criterion, balancing model fit and parsimony. Denominator df for fixed effects will be estimated using the Kenward-Roger approximation. The fitted mixed-effects model will be used to derive the model-estimated geometric mean titre at week 48 by back-transforming the least squares mean from the log scale, together with corresponding SEs and 95% CIs. The fixed-effect slope for the week 6 to week 48 interval will provide the estimated mean rate of change in log-transformed antibody titres during the waning phase, with corresponding 95% CIs. Results will be presented as model-estimated geometric mean titres with 95% CIs, estimated week 6 to week 48 slopes with 95% CIs and graphical displays of observed individual data with superimposed model-fitted trajectories over time.

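### The sample size is justified by a 90% CI of ±50 titre units, but the plan reports a 95% CI for a geometric mean from a log-scale model, so the stated precision does not describe the reported interval

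*Protocol article*

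**What the plan says.** The Sample size section sets the design target: "We aim to have a 95% chance of obtaining a 90% CI" "whose half-width is at most 50 GMT". Its variability input is "Assuming an expected SD of 485 GMT at week 48", taken from simulations on an earlier phase III trial's data. It concludes that "a sample size of approximately 300 participants would be required to achieve the desired level of accuracy around the mean GMT at week 48", and then "To account for a potential 9% dropout rate, 330 participants will be recruited across three clinical sites".

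The first primary endpoint is "Mean geometric OPXV-specific antibody titres at week 48 post vaccination with MVA-BN in a population recruited in Africa". The Primary endpoint analysis section fits a "linear mixed-effects model with log-transformed antibody titres as the dependent variable" and obtains the week 48 GMT by back-transforming the least squares mean. The results to be presented are "model-estimated geometric mean titres with 95% CIs, estimated week 6 to week 48 slopes with 95% CIs". The General principles section likewise refers to two-sided 95% intervals. A 90% interval is mentioned nowhere outside the sample size paragraph.

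**The concern.** The sizing statement and the analysis differ in two respects.

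- **Confidence level.** N is justified by a 90% interval; the reported intervals are 95%.
- **Scale.** The target is an additive half-width in titre units. The reported interval comes from a log-scale model, so it is multiplicative and asymmetric about the GMT. The section attaches the label GMT to both 50 and 485, but a GMT is a group summary and has no SD across participants. The inputs only work as an arithmetic mean and SD of titres. That is an inference from how the calculation behaves; the text does not say it outright.

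This is an estimation study without a hypothesis test, so the precision statement is its only quantitative design claim. If it stays as it is, readers will set the published 95% interval for the GMT against a benchmark built for a different interval on a different scale. The article gives neither a log-scale SD nor an expected GMT, so they cannot convert one to the other.

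**Working it through.** **Inputs.** From Sample size: 90% two-sided CI, 95% assurance, half-width h = 50, SD = 485, about 300 evaluable, 9% dropout, 330 recruited. From Primary endpoint analysis: log-transformed titres, back-transformed week 48 mean, 95% CI.

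**Step 1: reproduce the plan's figure.** Find the smallest n for which P(t × S/√n ≤ 50) ≥ 0.95, where t is the two-sided critical value on n − 1 df and (n − 1)S²/485² follows a chi-square distribution on n − 1 df.

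- 90% CI: n = 293. Requiring also that the interval captures the mean, as the section's wording suggests, again gives 293. The plan's figure of about 300 is consistent with this.
- Dropout: 300/0.91 = 329.7, rounded up to 330. This agrees.

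**Step 2: change only the confidence level, staying on the titre scale.** At n = 300, 485/√300 = 28.0.

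| Interval | Expected half-width | Half-width met with 95% assurance | P(half-width ≤ 50) |
|---|---|---|---|
| 90% CI | 1.650 × 28.0 = 46.2 | 49.3 | 0.978 |
| 95% CI | 1.968 × 28.0 = 55.1 | 58.8 | 0.011 |

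These figures are for an arithmetic mean, which is the scale of the sizing calculation but not the reported endpoint.

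**Step 3: translate to the GMT scale.** The document gives no log-scale SD and no expected GMT, so this step rests on an assumption: log-normal titres with arithmetic SD 485, and an arithmetic mean M varied over a range. Then

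- natural-log SD: s = √ln(1 + (485/M)²)
- GMT = M/√(1 + (485/M)²)
- 95% CI = GMT ×/÷ exp(t × s/√300), with t = 1.968
- half-width in titre units = half the distance between the two limits

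| M | GMT | s (log10 SD) | Factor each way | 95% CI | Half-width |
|---|---|---|---|---|---|
| 150 | 44 | 1.56 (0.68) | 1.19 | 37 to 53 | 7.9 |
| 300 | 158 | 1.13 (0.49) | 1.14 | 139 to 180 | 20.4 |
| 485 | 343 | 0.83 (0.36) | 1.10 | 312 to 377 | 32.5 |
| 700 | 575 | 0.63 (0.27) | 1.07 | 536 to 618 | 41.0 |
| 1000 | 900 | 0.46 (0.20) | 1.05 | 854 to 948 | 47.0 |
| 1300 | 1218 | 0.36 (0.16) | 1.04 | 1169 to 1269 | 50.0 |

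The same 300 participants and the same SD of 485 thus give half-widths from about 8 to 50 units, depending on a mean that the document does not state. At M = 150 a half-width of 50 would exceed the GMT itself (44); at M = 1000 it is about 6% of the GMT (50/900). A fixed figure of ±50 therefore carries no fixed meaning for the reported endpoint.

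These are simple one-sample intervals at week 48. The mixed model's interval may differ somewhat.

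**The case against.** The strongest reply is that the mismatch does no harm to the trial. Enrolment is complete, the model and its outputs are specified independently of the sample size paragraph, and no estimate changes. Planning at 90% and reporting at 95% is a difference to explain and does not invalidate the analysis. The sizing arithmetic is also correct. All of this stands, and it is why the point is a should-fix inconsistency.

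A reader might infer from the 1% in Step 2 that the reported interval will almost never meet the target, or that the study is too small. Sizing a 95% interval on the titre scale would indeed need 407 evaluable participants. The documents do not support either inference. The 1%, the 58.8 and the 407 all concern a 95% interval for an arithmetic mean, which the plan does not report as its primary result. For the GMT, Step 3 keeps the expected half-width inside 50 for arithmetic means from 150 to 1000, reaching 50 only near 1300. Nor can one say that a corrected statement would look less favourable: over that range it would look better in titre units.

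Three neighbouring matters are not part of this point: whether the SD of 485 carries over to the assay used here, which of the three antigens the figure refers to, and what precision the week 6 to week 48 slope will have. The first depends on a source not at hand. The others are separate matters or details that a condensed article may leave to the full protocol or the SAP.

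What the reply does not remove is the disagreement itself. The article states the sizing target, the model and the reported interval, and an SAP cannot make them agree unless one is changed or the link between them is explained.

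**Conclusion.** The point holds as an inconsistency between the sample size justification and the primary analysis; it is not an arithmetic error. The numbers 300 and 330 follow from their inputs, but they describe a 90% additive interval for an arithmetic mean, whereas the plan reports a 95% multiplicative interval for a GMT.

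- **Confidence level alone, on the protocol's own scale:** the chance of a half-width of 50 or less at n = 300 falls from 98% to about 1%, and the half-width met with 95% assurance is 58.8.
- **Scale:** there is no fixed direction. Under log-normality with SD 485 the expected 95% interval extends by a factor of about 1.19 down to 1.05 each way for arithmetic means of 150 to 1000.

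The first result rests only on the document's figures and the usual normal-theory assurance calculation. The second rests on the log-normal assumption and an assumed range of means. Neither shows that 330 participants are too few. Severity: should-fix.

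**What to change.** Keep N. In Sample size, state the precision for the interval that will be reported: with 300 evaluable participants, the two-sided 95% CI for the week 48 GMT is expected to extend by a factor of exp(1.96 × s/√300) each way. Here s is the natural-log SD, re-derived from the same simulations that produced the 485. As an illustration only, a log10 SD of 0.2 to 0.7 (an assumption; the document gives none) corresponds to ×/÷ 1.05 to 1.20:

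- exp(1.96 × 0.2 × 2.303/17.32) = 1.05
- exp(1.96 × 0.7 × 2.303/17.32) = 1.20

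Then either replace the existing statement of a 90% CI with half-width 50, or keep it labelled as a planning approximation for the arithmetic mean on the titre scale, and stop attaching the term GMT to the SD and the half-width.

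The cost is a rewritten paragraph and one rerun of the existing simulations on the log scale. No participants, visits or analyses change. Because N is already fixed, the restated figure should be presented as the precision expected from the enrolled sample, and not as a new basis for choosing it. It should be settled before the final data are seen; follow-up is anticipated to end in June 2026.
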